### Objectives and outcomes

The primary outcome is to test the feasibility of recruitment into a cohort embedded RCT in NEST of SRMs.

Secondary outcomes are as follows:Participant retention rate, measured annually by analysing the number of randomised participants retained and assessed with valid primary outcome data.Health-related quality of life, measured using the previously validated EuroQol -5domains-5levels (EQ-5D-5L) questionnaire prior to treatment and 3 months following treatmentTreatment complications, blood transfusion, intensive care unit admission, and renal replacement requirement rates, measured using clinical records during hospital admission, at 30 days postoperative and at 6 months.Length of hospital stay, time to return to pre-treatment activities and number of work days lost (in those who work), measured using clinical records and follow-up consultation (clinic or telephone) at 30 days and at 6 months.Costs incurred by health technologies, measured using NHS reference costs and also private and societal costs measured using patient completed questionnaire at time of treatment, at 30 days and at 6 months.

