**Methods and analysis:**

Single-centre prospective cohort study of adults diagnosed with SRM (n=200) with an open label embedded interventional RCT comparing nephron sparing interventions. Cohort participants will be managed at patient and clinicians’ discretion and agree with longitudinal clinical data and biological sample collection, with invitation for trial interventions and participation in comparator control groups. Cohort participants with biopsy-proven renal cell carcinoma eligible for both percutaneous cryoablation and partial nephrectomy will be randomly selected (1:1) and invited to consider percutaneous cryoablation (n=25). The comparator group will be robotic partial nephrectomy (n=25). The primary outcome of this feasibility study is participant recruitment. Qualitative research techniques will assess barriers and recruitment improvement opportunities. Secondary outcomes are participant trial retention, health-related quality of life, treatment complications, blood transfusion rate, intensive care unit admission and renal replacement requirement rates, length of hospital stay, time to return to pre-treatment activities, number of work days lost, and health technologies costs.

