### Interventions

Cohort participants eligible for the embedded RCT will be randomised 1:1 and invited to consider the trial intervention (percutaneous cryoablation). Randomisation will be performed in blocks of 10 participants through the online system ’Sealed Envelope' (www.sealedenvelope.com) to ensure allocation concealment. This will be an open label trial with unblinded outcome assessment.

The control group will be composed of participants treated with standard of care (partial nephrectomy). The trial intervention will be performed by interventional radiologists under CT guidance using argon probes to freeze and kill the tumour. The standard of care will be performed by urological surgeons with da Vinci robot assistance.

No restrictions will be placed on other clinically necessary concomitant care. Follow-up for the purposes of this feasibility trial will be 6 months, but standard clinical follow-up will be at least 5 years (table 1—visit schedule and assessments). On average, patients attend two clinic appointments prior to treatment. Post-treatment follow-up is based on histological findings at biopsy/surgery but usually involves 6 monthly clinic visits for a minimum of 5 years. Participants will not be required to have any additional visits, apart from volunteers for focus groups and structured interviews.

**Table 1 T1:** Visit schedule and assessments

Procedures	Visits								
	Screening	Baseline	Intervention	Week 4 post-intervention (only second stage of study)	Month 6 after baseline (first stage of study) or intervention (second stage of study)	Y1	Y2	Y3	Y5
Demographics		X							
Medical history		X							
Physical examination		X		X					
Consent		X	X						
Blood test		X		X	X	X	X	X	X
Imaging	X				X	X	X	X	X
Questionnaire		X		X	X	X	X	X	X
Cryoablation or partial nephrectomy			X						
Case report form		X	X	X	X	X	X	X	X
Adverse event reporting		X	X	X	X	X	X	X	X
Biobanking of blood/urine/tissue		X	X	X	X	X	X	X	X

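### Retention is defined through valid primary outcome data, but the primary outcome is recruitment, so that condition cannot measure attrition; the annual timing also falls outside the 6-month feasibility follow-up

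*Protocol article*

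**What the plan says.** The abstract states that "The primary outcome of this feasibility study is participant recruitment", and the section Objectives and outcomes says the same in other words: "The primary outcome is to test the feasibility of recruitment into a cohort embedded RCT in NEST of SRMs". No patient-level primary outcome is named.

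The first secondary outcome in that section is the retention rate, "measured annually by analysing the number of randomised participants retained and assessed with valid primary outcome data".

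The other secondary outcomes stop at 3 or 6 months. Quality of life by EQ-5D-5L is set before treatment and at 3 months. Complications and related event rates are "measured using clinical records during hospital admission, at 30 days postoperative and at 6 months". Hospital stay, return to activities, work days lost and costs also end at 6 months.

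On duration, the section Interventions says "Follow-up for the purposes of this feasibility trial will be 6 months, but standard clinical follow-up will be at least 5 years". Table 1 in that section has visits at month 6 and at years 1, 2, 3 and 5, each with a questionnaire, a case report form and adverse event reporting.

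The section on trial assessments and data collection foresees two kinds of departure. Some participants discontinue but stay on the follow-up schedule. Others stop follow-up altogether, in which case the data already collected are kept and analysed and the participant is not replaced.

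**The concern.** The retention definition would suit an effectiveness trial, where having valid primary outcome data means that the patient was still there to be measured. Here the primary outcome concerns entry to the trial and is settled near the start, so having it says nothing about whether the patient was followed afterwards.

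The section on sample size says the study is meant to inform the design, sample size and outcome measures of a multicentre trial. The attrition estimate feeds directly into that sample size. Loss may also differ between those who accept cryoablation, those who decline it, and controls who give no second consent. A rate without a clear numerator, denominator and time point would be a weak basis for planning.

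**Working it through.** The protocol gives no retention figure, target or dropout rate, so there is nothing to reproduce. The check compares the definition with the outcome and the follow-up it refers to, then illustrates the size.

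**1. What the primary-outcome condition excludes.** A participant not selected for the offer joins the control arm on the first-stage consent alone, so recruitment status is known at random selection. A participant selected for the offer has a known status once the invitation is answered, and a refusal is as valid a result as an acceptance. The condition therefore excludes nobody: with 50 randomised it is met by 50/50.

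**2. What remains.** Only *retained* can lower the rate. The article does not say whether it means not having withdrawn, still attending visits, or having data at a given time. It also does not say how to count a participant who discontinues but stays in follow-up, one who stops follow-up but whose data are kept, or one who declines the offer.

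**3. Illustration.** Inputs: n = 50 randomised (section on sample size); numbers lost k = 5, 10, 15 (assumed). Retention = (50 − k)/50. With x = 50 − k, the exact (Clopper-Pearson) 95% limits are the 0.025 quantile of Beta(x, n − x + 1) and the 0.975 quantile of Beta(x + 1, n − x).

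| Lost (assumed) | Primary-outcome condition alone | Retention if losses count | Exact 95% CI | Inflation = 1/retention |
|---|---|---|---|---|
| 5 | 50/50 = 100% | 45/50 = 90% | 78% to 97% | 1/0.90 = 1.11 |
| 10 | 50/50 = 100% | 40/50 = 80% | 66% to 90% | 1/0.80 = 1.25 |
| 15 | 50/50 = 100% | 35/50 = 70% | 55% to 82% | 1/0.70 = 1.43 |

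**4. Timing, if *annually* is counted per participant.** The first measurement is at 12 months, which is 12 − 6 = 6 months after the feasibility follow-up ends. The year-1 to year-5 visits make it possible, but outside that window.

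**5. Timing, if *annually* means calendar snapshots.** Inputs: 25 participants a year for 24 months (section on sample size), with accrual assumed uniform. Number with 6 months' follow-up at month t = 25/12 × (t − 6), up to 50.

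- Month 12: 25/12 × 6 = 12.5 of 25 enrolled, or 50%.
- Month 24: 25/12 × 18 = 37.5 of 50 enrolled, or 75%.
- Month 30: 25/12 × 24 = 50 of 50.

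These shares arise with no loss at all. They count follow-up from entry. Table 1 dates month 6 from the intervention in the second stage, so any wait for treatment would lower them. A yearly snapshot would mix participants not yet due with participants lost.

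**The case against.** The definition joins two conditions, and a participant who withdraws can reasonably be called not retained. A reader might infer that the metric returns 100% whatever happens. The text does not support that: it would be true only if *retained* added nothing, and the protocol expressly foresees participants who stop follow-up early. This objection stands, and the point is limited accordingly.

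The claim that recruitment status is known for everyone on the day of randomisation would also be too strong, because the offered group is selected first and consents later. The condition becomes empty once the invitation is answered.

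Nor is annual measurement impossible. Participants consent to long-term follow-up and Table 1 schedules later visits. That stands too, but those visits belong to standard clinical follow-up and lie beyond the window set for this feasibility trial.

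It can further be said that retention is not among the 12-month interim triggers (consent rate, complications and waiting time), that all analyses are exploratory, and that nothing bars a breakdown by arm. All of this is correct and lowers the weight of the point. That an operational criterion may sit in the full protocol or the analysis plan is a fair reason not to fault the silence on *retained* alone. It does not answer the main point, because the article states a measurement rule, and the part of the rule that is spelled out refers to the wrong kind of outcome.

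**Conclusion.** The point holds in a limited form. The primary-outcome condition is circular and cannot measure attrition, the rate therefore depends on an undefined word, and the annual timing does not fit the 6-month feasibility follow-up. The conclusion on circularity rests only on the article's own wording.

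The size is illustrative. The 90%, 80% and 70% depend on assumed losses, with 50 taken as the number randomised. The inflation factors of 1.11 to 1.43 follow from the same assumptions; they are not the correction of any figure in the protocol. The 50% and 75% snapshot shares assume uniform accrual and one of two readings of *annually*. The documents do not show that retention will be reported as 100%, or that differential loss will be hidden. They show that the definition as written does not ensure a usable attrition estimate. It is worth correcting, mainly because correction is cheap.

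**What to change.** Redefine retention as the proportion of all randomised participants, offered and not offered, with valid 6-month patient-level data: the 6-month complications record and the month-6 patient-completed questionnaire. State the date from which 6 months is counted, including for decliners who have neither trial treatment. Report the proportion by allocated arm and, within the offered arm, separately for acceptors and decliners, each with an exact 95% confidence interval. For scale, an assumed 40/50 gives 80% (66% to 90%); intervals for single arms will be wider.

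If EQ-5D-5L is the chosen questionnaire, first reconcile its 3-month time point in Objectives and outcomes with Table 1, which has questionnaires at week 4 and month 6 but no 3-month visit. Replace the annual timing with 6 months. Retention at the later yearly visits can be reported separately as long-term cohort follow-up.

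The cost is a change of wording and slight extra analysis, with no added visits, since the items are already scheduled at month 6. The resulting figure may be less favourable, partly because the data collection section says the post-procedure items will usually, not always, be assessed.

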### Trial assessments, data collection and data items

Case report forms (CRFs) will have either paper or electronic format. The CRFs will not bear the participant’s name or other directly identifiable data. The participant’s trial identification number (ID) only will be used for identification. All study-related procedures will be carried out during routine clinical visits. To maximise completeness of data, participants will also be asked for permission for research personnel to contact them via telephone. Quality control will be applied at each stage of data handling to ensure that all data are reliable and have been processed correctly. Completed CRFs will be checked for completeness and accuracy by designated individuals, against the source data. When the original CRFs are in paper format, they will be used when entering information into the computer database. The database will be checked against the CRFs for accuracy. No investigation of the data will begin until an accurate database has been assured. The CRFs will not bear the participant’s name or other directly identifiable data. The participant’s trial identification number (ID) only will be used for identification.

If a participant chooses to discontinue study participation, they should continue the follow-up schedule defined in the protocol, provided they are willing. However, if the participant confirms they do not wish to participate in the scheduled follow-up data collection visits, then data that have already been collected should be kept and analysed according to the intention-to-treat principle for all participants who stop follow-up early. Participants who stop the trial follow-up early will not be replaced.

Baseline data items include the following:medical and surgical history, including previous diagnosis of RCC-related hereditary syndrome, comorbidities and calculation of age corrected Charlson comorbidity index and performance status,current medication,allergies,physical examination, focused on abdomen (as per clinician discretion),baseline blood results (full blood count, renal function),renal tumour characteristics (complexity scoring, location, unifocality),body mass index, height and weight,occupation,ethnicity,family history of RCC or diagnosis of RCC-related hereditary syndrome,referral centre and date of referral,quality of life questionnaire (EQ-5D-5L).

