For patients who will not take part in the second stage of the study (intervention), subsequent assessments will be similar in frequency and content to post-intervention assessments (except for post-procedure assessment at 4 weeks).

The following data items will be assessed at time of intervention and immediately post-procedure:type of anaesthesia (general, sedation and local),operative complications,adverse events (AEs) during and post-procedure,routine blood tests post-procedure (as per clinician discretion),pain score post-procedure (daily),length of hospital stay.

The first post-procedure assessment happens face-to-face 4 weeks after surgery. The frequency of subsequent clinical assessments will be decided based on routine clinical follow-up. Subsequent assessments can be conducted face-to-face or via telephone, as per patient and clinicians’ discretion. In the majority of patients, this will happen every 6–12 months for 5 years. In the first post-procedure and each subsequent assessment, the following will usually be assessed:routine blood tests (as per clinician discretion),physical examination, focused on abdomen (as per clinician discretion),cross-sectional or ultrasound imaging (as per clinician discretion),complications,pain score,quality of life questionnaire (EQ-5D-5L).

In addition to standard of care diagnostic samples, biological samples obtained for research purposes will be obtained at each study visit in accordance with the consent form and patient information sheet. All participants will be asked to consent for the samples to be used for current and future ethically approved research. These will include blood, urine and tissue samples. Samples will be processed and stored indefinitely in pseudo-anonymised form centrally in accordance with all applicable legal and regulatory requirements, including the Human Tissue Act 2004 and any amendments thereafter.

After the end of the trial, participants will continue follow-up as per usual care.

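### The EQ-5D-5L outcome is set at 3 months after treatment, but the visit schedule has no 3-month collection in either arm

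*Protocol article*

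**What the plan says.** Under Objectives and outcomes, health-related quality of life is measured with the "EQ-5D-5L) questionnaire prior to treatment and 3 months following" treatment. The other timed clinical, recovery and cost outcomes in that list have their post-discharge measurements at 30 days and 6 months.

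Table 1 (Interventions) has two columns in the first half-year after treatment: "Week 4 post-intervention (only second stage of study") and "Month 6 after baseline (first stage of study) or intervention (second stage of study"). The questionnaire row is marked at both, and at baseline and years 1, 2, 3 and 5. The table has no month-3 column.

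The section on trial assessments follows the table. It states "The first post-procedure assessment happens face-to-face 4 weeks after surgery", puts later assessments at intervals of 6 to 12 months in most patients, and lists EQ-5D-5L among the items usually assessed at each.

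Two further statements limit other opportunities. Interventions says: "Participants will not be required to have any additional visits, apart from volunteers for focus groups and structured interviews". The assessments section says: "All study-related procedures will be carried out during routine clinical visits". Routine post-treatment follow-up "usually involves 6 monthly clinic visits for a minimum of 5 years".

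**The concern.** The article gives both a time point for this outcome and a full schedule for the instrument that measures it, and the two do not meet. This is a conflict between two stated rules, not a detail left to a longer document. An analysis plan can say how 3-month values will be analysed, but it cannot supply values that were not collected.

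The Sample size and recruitment section says the study is meant to inform the design, sample size and outcome measures of the full trial. If staff work from Table 1, EQ-5D-5L will have no data at its declared time, and the report will have to present week 4 or month 6 values under a definition that names neither. The study would also lose its chance to learn how completely the form is returned at 3 months.

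**Working it through.** No sample size, power or error rate is involved. The check compares the outcome definition with the schedule, using 3 months ≈ week 13 and 6 months ≈ week 26.

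| Source in the protocol article | EQ-5D-5L or questionnaire time points |
|---|---|
| Objectives and outcomes | before treatment; 3 months after |
| Table 1, questionnaire row | baseline; week 4; month 6; years 1, 2, 3, 5 |
| Trial assessments text | baseline; 4 weeks; then mostly every 6 to 12 months |

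1. **Does the table row cover EQ-5D-5L?** The row does not name an instrument, but the assessments text lists EQ-5D-5L at baseline, at the first post-procedure assessment and at each later one. The two sources agree on when it is given.
2. **Distance to the nearest collections.** Week 13 − week 4 = 9 weeks early. Week 26 − week 13 = 13 weeks late.
3. **Does it differ by arm?** No. One schedule serves cryoablation and partial nephrectomy, so the number of scheduled 3-month collections is 0 in each arm, across 25 + 25 = 50 planned participants.
4. **Does another statement supply a 3-month contact?** Routine visits are usually 6-monthly, and additional visits are not required except of qualitative volunteers. The article notes that "participants will also be asked for permission for research personnel to contact them via telephone", but gives no time for such contact. The interim criterion on complications at 90 days falls near 3 months, but it also has no matching visit and does not mention EQ-5D-5L.
5. **Do the other outcomes have the same problem?** The 30-day and 6-month points of the complication, recovery and cost outcomes correspond to the week 4 and month 6 columns. Among the timed secondary outcomes, quality of life is the one out of step.

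**The case against.** The strongest reply is that Table 1 is a schedule of visits and EQ-5D-5L does not need a visit. Participants consent at the first stage to completing questionnaires, the patient survey described questionnaires being sent, telephone permission is sought in order to maximise completeness, and later assessments may be by telephone. The wording on additional visits says only that they are not required. Visit frequency follows routine care, and the 6-to-12-month interval is given only for most patients. This stands to the extent that a reader might infer the 3-month value cannot be obtained at all, or will be missing for everyone. The documents do not support that: they show that none is scheduled, not that none could be collected. The reply does not remove the conflict, because the table has its own questionnaire row without a month-3 mark and study procedures are placed at routine visits.

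A reader might also infer that substituting week 4 or month 6 would shift the treatment difference or the SD carried into the full trial, or that the time point would be picked after unblinded results were seen. The article mentions rapid recovery after cryoablation, but it gives no EQ-5D-5L trajectory and no recovery times by arm, so neither the direction nor the size of a shift can be derived. Rules for time windows or substitution may be in documents not shown. Nor does the article establish that EQ-5D-5L is the only validated patient-reported measure: pain scores and a cost questionnaire are also collected, and it is silent on their validation.

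Finally, the primary outcome is recruitment, all analyses are exploratory, and none of the interim criteria uses EQ-5D-5L. That is correct and limits the importance of the point.

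**Conclusion.** The inconsistency is real and affects both arms equally. As written, the schedule contains no 3-month EQ-5D-5L for any of the 50 planned randomised participants, and the nearest collections are about 9 weeks early and 13 weeks late. The conclusion rests on reading Table 1 and the assessments text as the operating schedule. The flow chart and supplements are not shown, but the sections quoted conflict without them.

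The consequence is limited to one exploratory secondary outcome, and recruitment feasibility is unaffected. It should still be corrected, because the correction is cheap and a form not sent at 3 months cannot be recovered later.

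**What to change.** Reconcile Objectives and outcomes, Table 1 and the trial assessments text before data accrue, in one of two ways.

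- **Redefine the outcome at the collected time points:** pre-treatment, week 4 and month 6, with one post-treatment point named in advance as main. This needs only a wording amendment, adds no participant burden, and brings the outcome into line with the 30-day and 6-month points used elsewhere. The cost is giving up the stated 3-month measurement.
- **Keep 3 months and schedule it:** add an EQ-5D-5L by post or telephone for every randomised participant in both arms to Table 1 and to the assessments text, and amend the statement that confines study procedures to routine visits. This means about 50 extra forms and no clinic visit. The burden should be acknowledged: the patient survey asked about at most two questionnaires a year, while Table 1 already marks four from baseline to year 1 (baseline, week 4, month 6, year 1). A 3-month form would make five.
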